#### Efficacy analysis

All tests will be two-sided with significance set at *p* < .025 for each of the two primary endpoints and *p* < .01 for each of the secondary endpoints. Significance for all other tests will be set at *p* < .05. The analyses will be conducted blind to condition.

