### Aims and hypotheses

The aim of the current trial is to test the safety and efficacy of NAC as a pharmacotherapy for methamphetamine dependence using a double-blindplacebo-controlled randomised controlled trial. The trial will recruit 180 participants, who will receive either 12 weeks of oral NAC (2400 mg daily) or matched placebo. This is a phase IIb trial that is powered to confirm whether NAC has a clinically relevant benefit on methamphetamine use. The comparator condition is a matched placebo, with all participants provided with a minimal form of intervention (a self-help booklet), due to the lack of readily available standardised effective treatment options for methamphetamine use.

The primary hypothesis is that daily oral NAC delivered as a take-home medication will reduce methamphetamine use measured as (a) days of methamphetamine use and (b) methamphetamine-positive weekly saliva tests, during 12 weeks of active treatment relative to the placebo. The secondary hypotheses are that daily oral NAC delivered as a take-home medication will, relative to placebo:reduce the severity of methamphetamine dependence, the craving for methamphetamine, methamphetamine withdrawal symptoms and psychiatric symptoms (depressive symptoms, suicidality, psychotic symptoms and hostility)have an acceptable adverse event (AE) profilenot significantly increase the use of other substances (including alcohol, tobacco, cannabis, heroin and cocaine).

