##### Methamphetamine craving

Methamphetamine craving is assessed using the total score on the Craving Experience Questionnaire (CEQ), which has been validated for various substances [32]. The original CEQ has ten items: three items corresponding to the urge to use the substance, three items corresponding to intrusive thoughts and four items corresponding to the sensory aspects of substance use (e.g., picture, taste, smell and feel). The sensory items were adapted for methamphetamine and combined into three items: (1) taste and smell combined, (2) picturing methamphetamine and (3) imagining what it would feel like to smoke or inject it. This gave a total of nine items, each with scores ranging from 0 to 10 with higher scores representing a more severe craving.

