### Statistical considerations

#### Sample size estimation

The sample size of 90 participants per treatment arm is designed to detect a mean between-group difference of 3.5 days versus 6.0 days of methamphetamine use per month during the 12-week trial medication period with at least 80% power at *p* < 0.025 (0.05 / 2 to accommodate two primary outcome measures) and with 20% attrition (i.e., a final sample of at least 72 participants per treatment arm). The expected effect size is based on data from the Methamphetamine Treatment Evaluation Study (MATES) [42]. Participants who did not receive treatment in that cohort showed a reduction in methamphetamine use from a mean (standard deviation) of 12.8 (7.4) days per month at baseline to 6.0 (6.7) days per month at the 12-weekfollow-up. Our estimate of a minimal clinically meaningful reduction in use is based on outcomes for outpatient counselling derived from MATES: 11.2 (8.8) days per month to 3.5 (6.9) days per month at 12 weeks. Our estimate of 20% attrition is based on our previous research [42, 50, 51]. No interim analyses are planned. Statistical power was estimated using the SAMPSI command in Stata (Version 14.2, StataCorp LLC, College Station, Texas).

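### The fixed 0.025 level for each of the two primary measures is valid but needlessly conservative (Holm would do better), and the 0.01 secondary level should not be presented as family-wise control

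*Protocol article*

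**What the plan says.** The protocol article fixes three significance levels under Efficacy analysis. The sentence beginning "All tests will be two-sided with significance set at" gives p < 0.025 for each of the two primary endpoints and p < 0.01 for each secondary endpoint. The next begins "Significance for all other tests will be set at" and gives p < 0.05.

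Only the primary level is explained. Sample size estimation derives it as "0.05 / 2 to accommodate two primary outcome measures". No origin is given for 0.01, no family-wise target is stated for the secondary endpoints, and no stepwise procedure is named.

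The primary hypothesis (Aims and hypotheses) covers days of use and methamphetamine-positive saliva tests, and the Primary endpoint section treats these as two measures of one outcome. The secondary efficacy endpoints are craving, severity of dependence, withdrawal symptoms and "psychiatric symptoms (depressive symptoms, suicidality, psychotic symptoms and hostility". The last four each have their own definition under Psychiatric symptoms. Analysis of secondary outcomes gives every secondary outcome its own interaction test.

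**The concern.** Under the fixed rule, the result on one primary measure has no bearing on the level used for the other. Once one measure is significant, the other could be tested at 0.05 within the same 5% family-wise guarantee, but the plan keeps it at 0.025. This matters because one measure is self-report and the other biological. Agreement between them is what would make a positive result convincing, and it is there that the fixed rule loses power.

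For the secondary endpoints, a level stricter than 0.05 that follows an explicit Bonferroni split for the primaries can look like multiplicity control. A reader of the results could then take a secondary finding at p < 0.01 as protected at 5% over the whole set, which the threshold does not guarantee.

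**Working it through.** **The plan's own figure.** 0.05 / 2 = 0.025. Conversely 2 × 0.025 = 0.05, which bounds family-wise error under any correlation; if the tests are independent, 1 − 0.975² = 0.0494. The primary rule reproduces and is valid.

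**Holm for two measures.** Test the smaller p against 0.025; if it passes, test the larger against 0.05.

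- Both nulls true: a false rejection needs the smaller p below 0.025, with probability at most 2 × 0.025 = 0.05.
- One null true: rejecting it needs its own p below 0.05, with probability at most 0.05.
- The first step is the Bonferroni step, so the chance of at least one rejection is identical, and anything Bonferroni rejects Holm also rejects.

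**Power, independent measures.** Assume 80% power for each measure at two-sided 0.025. The article claims at least 80% for days of use and gives no figure for saliva.

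- Power at 0.05: Φ(2.241 + 0.842 − 1.960) = Φ(1.123) = 0.869.
- Both significant, fixed rule: 0.80² = 0.64.
- Both significant, Holm: both below 0.05 and at least one below 0.025, so 0.869² − (0.869 − 0.80)² = 0.755 − 0.005 = 0.75.
- Each measure, Holm: 0.80 + 0.069 × 0.80 = 0.855.

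**Power, correlated measures.** Simulation with 200,000 draws of normal test statistics; the correlations are assumed, as the article gives none.

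| Correlation | Both, fixed 0.025 | Both, Holm | Each, Holm | At least one (either rule) |
|---|---|---|---|---|
| 0 | 64% | 75% | 86% | 96% |
| 0.3 | 67% | 77% | 85% | 93% |
| 0.5 | 69% | 78% | 85% | 91% |
| 0.8 | 73% | 80% | 84% | 87% |

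The gain does not hinge on 80%. As a sensitivity case, take a standardised shift of 2.5 / (6.80 × √(2/72)) = 2.21, from the article's means, its pooled standard deviation (√((6.7² + 6.9²)/2) = 6.80) and 72 per arm in a plain two-sample comparison. Each measure then has about 49% power, and power for both rises from 24–38% to 34–48%. The planned analysis uses repeated measures, so this is not a statement about the trial's actual power.

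**What Holm costs.** If only one measure has a true effect, the chance of wrongly rejecting the other rises from 2.5% to about 3.9–4.5%, still within 5%. If the second p lies between 0.025 and 0.05, Holm rejects while a 97.5% interval includes no effect.

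**Secondary endpoints.** The count is craving, dependence, withdrawal and four psychiatric endpoints: 3 + 4 = 7. (Not increasing other substance use is a secondary hypothesis but is placed under Other assessments, so it is left out; including it would give 8 × 0.01 = 0.08.)

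- Upper bound: 7 × 0.01 = 0.07.
- Independent: 1 − 0.99⁷ = 0.068.
- Simulated, equal correlation of 0.3, 0.5 and 0.8: 0.063, 0.055 and 0.037.

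Holm over seven at 0.05 uses 0.0071, 0.0083, 0.0100, 0.0125, 0.0167, 0.025 and 0.05. It is stricter than 0.01 at the first two steps, equal at the third and looser at the last four. A lone true effect with 80% power at 0.01 falls to about 77%. If all seven effects are real and each has 80% power at 0.01, power per endpoint rises to 84–89%.

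**The case against.** The strongest reply is that nothing here is wrong. The primary rule is pre-specified, holds 5% under any dependence, agrees with the sample-size alpha and keeps tests consistent with 97.5% intervals. Holm does not raise the chance of at least one primary success. All of that stands. A reader might infer that the primary thresholds are a flaw in error control; the document does not support that reading. The case for Holm is efficiency.

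On the secondary endpoints, a reader might infer that 0.01 was meant as 0.05 / 5, so that two endpoints were missed and a 5% target fails. The document does not support this either. It writes out the division for the primaries and gives none for the secondaries, and 0.01 may simply be a stricter conventional level. The 7% is also a ceiling: four of the seven endpoints come from one rating scale and the other three concern the same drug in the same people, so positive correlation is likely. Under strong correlation the rate falls below 5%. What remains is that the basis of 0.01 is unstated and that it guarantees no 5% limit over seven tests.

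It can also be said that the statistical analysis plan may settle this. The article does defer final details, including imputation and covariates, to that plan. The significance levels, however, are stated outright in the article, and a plan that repeats them would carry the point forward.

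**Conclusion.** The point holds as a recommended improvement for the primary measures and a clarification for the secondary endpoints.

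For the primaries, Holm keeps the 5% guarantee and adds roughly 8 to 11 percentage points to the power to confirm both measures. This assumes 80% power for each at 0.025, equal effects in standardised terms and a correlation between 0 and 0.8. The saliva power is an assumption throughout. The improvement is nearly free but not wholly so, because test and interval can disagree for the second measure.

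For the secondaries, family-wise error under 0.01 is at most 7%, 6.8% under independence and less under positive correlation. That is a modest excess over a target the article never sets. It would be tempting to say that Holm repairs both sets at no cost. For the secondaries it is a trade-off, and Holm applied within each set separately does not control error across primaries and secondaries together.

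**What to change.** **Primary measures.** State in the statistical analysis plan that the two are tested with Holm's procedure at family-wise two-sided 0.05: the smaller p against 0.025 and, if significant, the larger against 0.05. Leave the sample-size alpha at 0.025. If 97.5% intervals are reported, state that the Holm test governs the conclusion when the two disagree.

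**Secondary endpoints.** List the seven endpoints and choose one of two statements:

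- Keep 0.01 as a stricter per-test level and say that it is not family-wise control.
- If 5% control over the seven is wanted, use Holm at 0.05 and accept the stricter first two steps (0.0071 and 0.0083).

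**Cost.** The change is wording only; recruitment, visits and data collection are unaffected. The article says the analysis plan will be written before unblinding and reports 77 of 180 participants randomised by 9 May 2019. The change should be made and dated before unblinding.

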##### Analysis of primary outcomes

Intention-to-treat analyses will be conducted for the primary outcomes. The effect of the trial medication on days of methamphetamine use (percentage of days used in the past 28 days) will be tested using a baseline (assessment 0) vs. medication phase (three repeats: assessments 4, 8 and 12) by treatment condition (NAC vs. placebo). Unobserved days (e.g., due to hospitalisation or incarceration) will be censored. The effect of NAC on methamphetamine-positive saliva will be tested using a main effect for treatment condition (NAC vs. placebo) on saliva test results (positive vs. negative) from assessments 1–12 (12 repeats).

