##### Analysis of secondary outcomes

Analysis of secondary outcomes will be based on a modified intention-to-treat dataset that includes only participants who completed assessment 0 and at least one follow-up assessment (i.e., assessments 1–12). The effect of NAC on each secondary outcome will be tested using a baseline (assessment 0) vs. medication phase (assessments 1–12) by treatment condition (NAC vs. placebo) interaction.

All effects will be tested with mixed effects models with repeated measures for each measurement time point. Heterogeneity in variance and treatment effect between sites will be tested for by seeing whether the model fit is significantly improved by including a random intercept for site and a random coefficient for the main effect by site, respectively. If no significant heterogeneity is found, the more parsimonious model will be retained. Missing data will be imputed using multiple imputation by chained equations implemented in Stata in the analysis of the primary outcomes only. Final details of the analysis, including methods of imputation and covariates, will be outlined in a statistical analysis plan prior to unblinding of the data. An additional statistical plan for a health economic evaluation will be developed prior to undertaking any such analysis.

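### The days-of-use primary test is, on its ordinary reading, a difference in change from baseline; it is valid, but a baseline-adjusted comparison of the same data is more precise

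*Protocol article*

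**What the plan says.** Under Analysis of primary outcomes, the effect on days of use, expressed as a percentage over 28-day windows, "will be tested using a baseline (assessment 0) vs. medication phase (three repeats: assessments 4, 8 and 12) by treatment condition (NAC vs. placebo"). The word interaction is absent there, but Analysis of secondary outcomes uses it for the same structure: each secondary outcome is "tested using a baseline (assessment 0) vs. medication phase (assessments 1–12) by treatment condition (NAC vs. placebo) interaction". The saliva outcome, by contrast, is tested by a main effect of treatment. On the model, the protocol says "All effects will be tested with mixed effects models with repeated measures for each measurement time point". It then adds that "Final details of the analysis, including methods of imputation and covariates, will be outlined in a statistical analysis plan".

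Sample size estimation describes the trial as "designed to detect a mean between-group difference of 3.5 days versus 6.0 days of methamphetamine use per month during the 12-week trial medication period". The power claimed is 80% or more at a level of 0.025, which is 0.05 split over the two primary measures, and 72 per arm are expected to be analysed once a fifth have dropped out. The same section gives means and SDs at baseline and at 12 weeks for two cohorts, but no correlation between repeated measurements.

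Table 1 shows timeline followback data at assessment 0, and the Trial medication section has the first bottle handed over at that visit. Assessment 0 is therefore a pre-dose measurement in randomised arms.

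**The concern.** In a model with phase, treatment and their interaction, and with complete data, the interaction estimate is the mean of assessments 4, 8 and 12 minus assessment 0, compared between arms. The single baseline value is subtracted with weight 1, noise included. Because assessment 0 precedes the first dose, the two arms share the same true mean at that visit. Estimating two separate baseline means gives up that information.

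There are two consequences. An effect of the planned size is more likely to be missed than these data require. And in any one trial the estimate moves with chance baseline imbalance: the arm that happens to start higher tends to appear to improve more.

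**Working it through.** **Inputs** (Sample size estimation, Efficacy analysis): difference 6.0 − 3.5 = 2.5 days; follow-up SDs 6.7 and 6.9; baseline SDs 7.4 and 8.8; 72 per arm (90 × 0.8); two-sided 0.025, critical value 2.241. Mean follow-up variance: (6.7² + 6.9²)/2 = 46.25. The correlation ρ is assumed: 0.3, 0.5 or 0.7, first taken as equal between all pairs of visits. Power is Φ(2.5/SE − 2.241). Working in days or in percentage of days does not affect power.

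**1. The plan's own figure.** For one follow-up value without baseline, SE = √(2 × 46.25/72) = 1.133 and power = Φ(2.206 − 2.241) = 48.6%. The printed inputs alone do not give 80%. The Stata command named allows repeated measures with a correlation, which the article does not report, so the stated power is neither reproduced nor shown to be wrong.

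**2. Equal SDs at baseline and follow-up.** Per-person variance as a multiple of the follow-up variance:
- interaction (change): (1 + 2ρ)/3 + 1 − 2ρ = 4(1 − ρ)/3
- baseline-adjusted: (1 + 2ρ)/3 − ρ² = (1 − ρ)(1 + 3ρ)/3
- ratio, adjusted to interaction: (1 + 3ρ)/4, so the variance reduction is 3(1 − ρ)/4

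Example, ρ = 0.5: the factors are 0.667 and 0.417. The SEs are √(92.5 × 0.667/72) = 0.925 and √(92.5 × 0.417/72) = 0.732. Power is Φ(2.701 − 2.241) = 68% and Φ(3.417 − 2.241) = 88%.

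**3. Printed baseline SDs.** With follow-up SD s and baseline SD b, the change variance in each arm is s²(1 + 2ρ)/3 + b² − 2ρsb. At ρ = 0.5 this is 35.1 (6.7, 7.4) plus 48.5 (6.9, 8.8), total 83.6. SE = √(83.6/72) = 1.077 and power is 53%. The adjusted total stays at 92.5 × 0.417 = 38.5, so the reduction is 1 − 38.5/83.6 = 54%.

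| ρ | Variance reduction, equal SDs | Variance reduction, printed SDs | Power, interaction, equal SDs | Power, interaction, printed SDs | Power, adjusted |
|---|---|---|---|---|---|
| 0.3 | 52.5% | 64% | 52% | 40% | 86% |
| 0.5 | 37.5% | 54% | 68% | 53% | 88% |
| 0.7 | 22.5% | 45% | 89% | 76% | 96% |

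The interaction reaches 80% power only from ρ of about 0.62 (equal SDs) or 0.73 (printed SDs).

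**4. Outside these assumptions.** With equal SDs the reduction is 67.5% at ρ = 0.1 and 7.5% at ρ = 0.9. If baseline correlates 0.4 with each follow-up while follow-ups correlate 0.6 with each other, the factors are 0.733 + 1 − 0.8 = 0.933 and 0.733 − 0.16 = 0.573, giving 52% against 75% power.

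**5. Chance imbalance.** In 6,000 simulated trials per correlation (normal data, 72 per arm, equal SDs), the interaction estimate moved by −0.71, −0.49 and −0.29 days per day of baseline difference at ρ = 0.3, 0.5 and 0.7, close to −(1 − ρ). The adjusted estimate moved by about 0.01 or less. Averaged over all trials, both were unbiased. The simulated variance reductions were 52%, 36% and 21%, in line with the formula.

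**6. Continuous secondary outcomes.** With 12 repeats, equal SDs and exchangeability, the ratio is (1 + 12ρ)/13, for example 0.54 at ρ = 0.5.

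**The case against.** The strongest objection is that the protocol never says a treatment main effect is in the model. A common-baseline model also tests a phase-by-treatment term, only without separate baseline means, so the wording does not exclude it, and final details are left to an analysis plan that is not shown. This stands in part: the point cannot be that the protocol forbids the better form. But nothing in the text signals the constraint, and the ordinary reading of such an interaction is the one with separate baselines.

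Four stronger readings are tempting, and the documents support none of them.

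- *The trial is powered for one quantity and tests another.* The planning cohorts differ by 2.5 days in level at 12 weeks but by only 0.9 in change (7.7 versus 6.8), because their baselines were 11.2 and 12.8. In a randomised trial the true baseline means are equal, so the true difference in change equals the difference in level. Only the variance differs.
- *The planned test is biased.* It is not. The shift is conditional on the imbalance that happens to occur.
- *A fixed share of precision is lost.* Any percentage depends on a correlation that the documents do not give.
- *Adjustment guarantees 80% power.* It stays above 85% for every exchangeable correlation, but falls to 75% in the 0.4/0.6 case.

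Days of use are also bounded and probably skewed (mean 3.5, SD 6.9). If a non-linear mixed model is used, the formulas are only approximate. The psychiatric endpoints are binary, and the closed-form gain does not cover them.

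**Conclusion.** The point holds as one of efficiency. The planned test is valid but, on its ordinary reading, weaker than it needs to be. For exchangeable correlations of 0.3 to 0.7, adjustment would cut the variance by 22.5% to 52.5% with equal SDs, and by about 45% to 64% with the protocol's printed baseline SDs. The power gain is largest at low correlation (52% to 86% at 0.3) and small at high correlation (89% to 96% at 0.7), both with equal SDs. These figures assume complete data on 72 per arm and a linear model. The ordering does not depend on the exact correlation: with k the ratio of baseline to follow-up SD, the variance factors differ by (k − ρ)². That is positive for any ρ below 1 when k is 1, and also at the printed ratios of 1.10 (7.4/6.7) and 1.28 (8.8/6.9).

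**What to change.** In Analysis of primary outcomes, keep assessments 0, 4, 8 and 12 as outcomes in the mixed model. Constrain the two arms to a common mean at assessment 0 (no treatment main effect at baseline), use an unstructured covariance so that baseline has its own variance, and test the treatment effect averaged over assessments 4, 8 and 12. Alternatively, model assessments 4, 8 and 12 with the assessment 0 value as a covariate. The two are close but not identical when data are missing, so the text should name one.

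Use the same form for the continuous secondary outcomes over assessments 1–12. For the binary psychiatric endpoints, adjust for the assessment 0 value without claiming the gain computed here.

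The cost is a sentence for each set of outcomes, fixed before unblinding. No data, visits or participants are added. The only added assumption in the constrained model is equal true means at assessment 0, which randomisation and the pre-dose timing of that visit justify.

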##### Analysis of secondary outcomes

Analysis of secondary outcomes will be based on a modified intention-to-treat dataset that includes only participants who completed assessment 0 and at least one follow-up assessment (i.e., assessments 1–12). The effect of NAC on each secondary outcome will be tested using a baseline (assessment 0) vs. medication phase (assessments 1–12) by treatment condition (NAC vs. placebo) interaction.

All effects will be tested with mixed effects models with repeated measures for each measurement time point. Heterogeneity in variance and treatment effect between sites will be tested for by seeing whether the model fit is significantly improved by including a random intercept for site and a random coefficient for the main effect by site, respectively. If no significant heterogeneity is found, the more parsimonious model will be retained. Missing data will be imputed using multiple imputation by chained equations implemented in Stata in the analysis of the primary outcomes only. Final details of the analysis, including methods of imputation and covariates, will be outlined in a statistical analysis plan prior to unblinding of the data. An additional statistical plan for a health economic evaluation will be developed prior to undertaking any such analysis.

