#### Trial medication

Trial medication bottles are distributed to the trial site pharmacy in batches. On dispensing, the adhesive label indicating treatment allocation is removed by the pharmacist and placed in the participant’s pharmacy file. Trial medication is provided to the trial researcher who delivers the medication to the participant at assessment 0. Medication bottles are replaced at 3-week intervals. Participants are provided with feedback on their medication adherence at each assessment using eCAP™ technology (Med-ic eCAP™, Information Mediary Corp, see Adherence for details). The number of capsules remaining in each medication bottle is audited on return.

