#### Discontinuation of medication and withdrawal from the trial

Participants are free to discontinue the trial medication or withdraw from the study at any time. Investigators may discontinue trial medication or withdraw a participant from the trial for the following reasons: pregnancy, no longer meeting the inclusion criteria, failing to take the medication for 7 or more days, significant non-compliance with the study protocol, disease progression that requires discontinuation of the trial medication or a clinical condition for which it would not be in the best interest of the participant to continue taking the trial medication. Follow-up assessments are completed regardless of medication discontinuation for all participants who remain consented into the study.

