#### Secondary endpoints

All secondary outcomes are assessed for the past week at assessments 0 to 12.

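### Secondary outcomes are analysed in a narrower set than the primary outcomes, a restriction that the planned mixed model does not need and that discards observed data

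*Protocol article*

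**What the plan says.** All places are in the protocol article.

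- **Primary outcomes** (Analysis of primary outcomes): "Intention-to-treat analyses will be conducted for the primary outcomes".
- **Secondary outcomes** (Analysis of secondary outcomes): a "modified intention-to-treat dataset that includes only participants who completed assessment 0 and at least one follow-up assessment". No exception and no reason is given. Under Secondary endpoints the rule covers craving, severity of dependence, withdrawal and the four psychiatric endpoints.
- **Schedule** (Secondary endpoints): "All secondary outcomes are assessed for the past week at assessments 0 to 12".
- **Contrast** (Analysis of secondary outcomes): each secondary effect is "tested using a baseline (assessment 0) vs. medication phase (assessments 1–12) by treatment condition (NAC vs. placebo) interaction".
- **Model** (same section): "All effects will be tested with mixed effects models with repeated measures for each measurement time point".
- **Missing data** (same section): "Missing data will be imputed using multiple imputation by chained equations implemented in Stata in the analysis of the primary outcomes only".
- **Start of medication** (Trial medication): "Trial medication is provided to the trial researcher who delivers the medication to the participant at assessment 0".
- **After stopping medication** (Discontinuation of medication and withdrawal from the trial): "Follow-up assessments are completed regardless of medication discontinuation for all participants who remain consented into the study".

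The article leaves imputation methods and covariates to a later analysis plan, but it fixes the secondary analysis set itself.

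**The concern.** Whether a participant attends any of assessments 1-12 is known only after allocation. Conditioning on it replaces the randomised groups with groups selected afterwards, and the secondary results then describe a different population from the primary result.

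The rule discards two kinds of observed data: the baseline value of anyone with no follow-up visit, and every follow-up value of anyone without assessment 0. Secondary outcomes have no imputation to make up for either.

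The model does not require this. A likelihood-based mixed model with assessment 0 among the repeats accepts incomplete records and is valid when data are missing at random. The primary days-of-use analysis already sets assessment 0 against the medication phase by treatment, under intention to treat. What is at stake is a possible small distortion of the secondary comparisons and an avoidable mismatch of populations.

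**Working it through.** **1. How many could be removed.** The only loss figure in the article is the planned attrition under Sample size estimation: 90 × (1 − 0.20) = 72 per arm, which reproduces. That is total attrition, not loss before a first follow-up, so early loss has to be assumed. Of 180 randomised:

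| Assumed early loss | Participants removed |
|---|---|
| 2% | 180 × 0.02 = 3.6 |
| 5% | 9 |
| 10% | 18 |
| 20% (all planned attrition before assessment 1) | 36 |

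**2. Hand calculation on assumed figures.** Suppose 8 of 90 NAC and 2 of 90 placebo participants have no follow-up. Their baseline is 1 SD above (worse than) their arm's mean, the baseline to follow-up correlation is 0.5, and there is no true effect.

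- Baseline mean of those kept: NAC −8/82 = −0.098 SD; placebo −2/88 = −0.023 SD.
- Their follow-up mean shifts by 0.5 times that, so the change from baseline shifts by (0.5 − 1) times that.
- Bias in the interaction: (0.5 − 1) × (−0.098 + 0.023) = +0.037 SD.

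Standard error for comparison, with 12 follow-ups and a common correlation of 0.5:

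- Variance of the follow-up mean: (1 + 11 × 0.5)/12 = 0.542.
- Variance of the change: 0.542 + 1 − 2 × 0.5 = 0.542.
- SE: √[0.542 × (1/82 + 1/88)] = 0.113 SD.

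The bias is 0.037/0.113 = 0.33 SE. At the article's two-sided 0.01 level for secondary endpoints, the false-positive rate becomes P(Z > 2.576 − 0.33) + P(Z < −2.576 − 0.33), about 1.2% + 0.2% = 1.4%. The larger part lies against NAC, because higher scores are worse on these scales.

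**3. Simulation.** Continuous outcome in SD units, 90 per arm, correlation 0.5, no true effect, 4,000 runs. Base loss is the probability of no follow-up at an average baseline. Where loss is related to baseline, its log-odds change by 1 per SD. Bias is NAC minus placebo.

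| Base loss, NAC / placebo | Relation to baseline | Mean number kept | Bias, modified set | Bias, all randomised |
|---|---|---|---|---|
| 5% / 5% | none | 171.0 | 0.000 | 0.000 |
| 10% / 10% | same in both arms | 156.0 | −0.001 | −0.002 |
| 5% / 5% | NAC only | 168.9 | 0.032 | −0.002 |
| 10% / 5% | NAC only | 163.4 | 0.061 | 0.002 |
| 20% / 10% | NAC only | 149.4 | 0.101 | −0.002 |
| 10% / 10% | opposite in the two arms | 155.9 | 0.118 | −0.002 |
| 20% / 20% | opposite in the two arms | 137.0 | 0.207 | 0.003 |

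The last row removes 180 − 137 = 43 participants before any follow-up, more than the 36 of the whole planned attrition, so it is an extreme. Precision is about the same either way: the SD of the estimate is 0.112 to 0.119 with all randomised participants and 0.113 to 0.122 with the modified set.

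**4. What this does not cover.** In every scenario loss depends only on the observed baseline, and everyone kept has complete follow-up. Loss that depends on unobserved outcomes was not simulated. Nor were the psychiatric endpoints, which are binary (item-score thresholds under Psychiatric symptoms).

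**The case against.** The strongest case on the other side is that the set is prespecified, openly labelled as modified, confined to secondary outcomes and leaves the primary conclusion untouched. A participant with no follow-up contributes one baseline value, and the bias is a fraction of a standard error even on figures chosen to produce it. All of that stands, and it limits the weight of the point. It does not supply a reason for the restriction.

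Several stronger readings are tempting, and the documents do not support them.

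- **That the fix would cure bias from poor tolerability.** Tolerability is experienced after assessment 0. If loss depends on it, or on outcomes never seen, a baseline value does not repair the comparison.
- **That everyone who stops medication early is removed.** Follow-up continues after stopping for those still consented, and one attended visit after assessment 0 is enough to stay in the set.
- **That a safety signal on suicidality or psychosis is hidden.** These endpoints enter as hypotheses of benefit. Adverse events are a separate measure, and the rule is not stated to apply to them.
- **That missing assessment 0 reflects a reaction to treatment.** Medication is first handed over there, under blinding, so this is unlikely. The article also does not say outright that randomisation comes before assessment 0; that is inferred from dispensing by allocation before the hand-over. The objection to this half of the rule is the loss of follow-up values.
- **That the rule favours NAC.** In the hand calculation it works against NAC. The sign depends on which arm loses which participants.

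**Conclusion.** The concern holds as a minor point. The article fixes a secondary analysis set that is narrower than the primary one, is defined by events after randomisation, and is not needed by its own model. The consequence is probably small: near zero if early loss is unrelated to baseline or related to it equally in both arms, and about 0.03 to 0.06 SD if 5-10% early loss is related to baseline in one arm only (0.061/0.113 = 0.54 SE at the upper end). Larger values need heavier early loss or opposite selection in the two arms. These sizes rest on an assumed early loss, a correlation of 0.5, a continuous outcome and loss that depends only on the observed baseline. No size is claimed for the binary psychiatric endpoints.

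**What to change.** State in the analysis plan, before unblinding, that secondary outcomes are analysed in all randomised participants as randomised. Every available value from assessments 0-12 should enter the same likelihood-based mixed model, including participants with only a baseline value or only follow-up values. Keep the modified set as a sensitivity analysis, and report by arm how many participants it removes. The plan should say that the main analysis assumes data missing at random and does not deal with loss driven by tolerability or unobserved outcomes.

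The cost is about one sentence. It needs no new data and no more participants, and precision in the simulation was no worse.
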